## Abstract

**Background:**

Chordomas of the skull base are relative rare lesions of the bones. Surgical resection is the primary treatment standard, though complete resection is nearly impossible due to close proximity to critical and hence also dose limiting organs for radiation therapy. Level of recurrence after surgery alone is comparatively high, so adjuvant radiation therapy is very important for the improvement of local control rates. Proton therapy is the gold standard in the treatment of skull base chordomas. However, high-LET beams such as carbon ions theoretically offer biologic advantages by enhanced biologic effectiveness in slow-growing tumors.

**Methods/design:**

This clinical study is a prospective randomised phase III trial. The trial will be carried out at Heidelberger Ionenstrahl-Therapie centre (HIT) and is a monocentric study.

Patients with skull base chordoma will be randomised to either proton or carbon ion radiation therapy. As a standard, patients will undergo non-invasive, rigid immobilization and target volume delineation will be carried out based on CT and MRI data. The biologically isoeffective target dose to the PTV in carbon ion treatment (accelerated dose) will be 63 Gy E ± 5% and 72 Gy E ± 5% (standard dose) in proton therapy respectively. Local-progression free survival (LPFS) will be analysed as primary end point. Toxicity and overall survival are the secondary end points. Additional examined parameters are patterns of recurrence, prognostic factors and plan quality analysis.

**Discussion:**

Up until now it was impossible to compare two different particle therapies, i.e. protons and carbon ions directly at the same facility.

The aim of this study is to find out, whether the biological advantages of carbon ion therapy can also be clinically confirmed and translated into the better local control rates in the treatment of skull base chordomas.

**Trial registration:**

ClinicalTrials.gov identifier: NCT01182779

## Background

Chordomas (1 - 4% of all malignant bone tumors) of the skull base are relative rare lesions of the bones. The incidence is around 100 new cases per year in Germany and 0.08/100000 in the US corresponding to around 300 new cases per year [1]. Chordomas arise from embryonic remnants of the notochord and are found at the base of the skull area in 35% of all cases. According to the histopathological findings, chordomas are divided into conventional (most common), chondroid and dedifferentiated types [2,3]. Histological differentiation between chordomas and chondrosarcomas is difficult and must contain immunhistochemical tests [4]. Chordoma is immunopositive for epithelial markers like cytokeratin and endothelial membrane antigen (EMA), whereas chondrosarcoma is negative for both. Both chordomas and chondrosarcomas can be positive for S-100 and vimentin.

The average age at the diagnosis is 49 years for base of skull localization. Also, the base of the skull is the most common localisation of chordomas in children and adolescents. In children and adolescents chordomas may behave more aggressively [5]. Men are affected more frequently than women.

Surgical resection is the primary treatment standard, though complete resection is nearly impossible due to close proximity to critical and hence also dose limiting organs for radiation therapy i.e. optic nerves, chiasm and brainstem. Level of recurrence after surgery alone is with reported rates between 50% and 100% [6] comparatively high, so adjuvant radiation therapy is very important for the improvement of local control rates in the primary treatment even after complete resection. Tumour volume is an important prognostic factor, hence a tumour debulking is usually required before radiation therapy application [7]. Other prognostic relevant risk factors are the histological tumour type, resection status, gender, and the age of the patient [8,9].

Radiation resistance is a common characteristic of chordomas [10,11], so high total doses are needed to achive acceptable local control rates after radiotherapy. Conformal precision and image guided radiation therapy techniques provide a safe technique for dose escalation [12]. The physical characteristics of carbon ions or protons such as inverted dose profile allow steep dose gradients and therefore provide further benefit in this field by potentially reducing toxicity.

So far, proton therapy is the gold standard in treatment of rare skull-base tumours like chordoma and low grade chondrosarcoma. The Loma Linda University Medical Center (LLUMC) [13] and the Massachusetts General Hospital (MGH) in Boston [14] have the largest experience in particle therapy for these entities. 3-year local control for chordomas after fractionated proton radiation therapy in 33 patients at LLUMC was 67% and the actuarial 5 year survival rate was 79% respectively [14]. The outcome of 519 cases of chordomas and chondrosarcomas of the skull base including 290 chordomas treated with a combination of proton and photon therapy at MGH/HCL shows a significant difference in local control and survival rates between the patients with chordoma and chondrosarcoma. 5- and 10-year local progression free survival was 98% and 94% for chondrosarcomas and 73% and 54% for chordomas [13,14].

Proton therapy results from PSI in Villingen, Switzerland were published by Weber et al. and showed 3 year local control rates of 87.5% for chordomas. However, the treated tumour volumes with a median GTV of 16.4 ml were relatively small. 29 patients, among them 18 patients with chordoma were treated to a median target dose of 74 GyE. The 3-year actuarial PFS rate for the entire patient cohort was 90% [15].

Carbon ions though, have a higher biological effectiveness than either protons or photons, which might improve the results of these radio-resistant tumours [16]. Carbon ion therapy is available only at the National Institute of Radiological Sciences (NIRS) in Japan and up to July 2008 has been available at the Gesellschaft für Schwerionenforschung (GSI) Darmstadt in Germany. The experience of our Japanese colleagues is limited to 40 patients with chordoma and chondrosarcoma of the skull base who could be treated effectively and without serious side effects [17]. NIRS beam delivery technique relies on passive scanning necessitating various modulators to adjust for treatment depth and tissue inhomogeneities within the beam path.

In comparison to the Japanese centres, the facility at GSI as well as the Heidelberger Ionenstrahl-Therapie centre (HIT) relies on active beam delivery using the raster-scan technique. In prior series, each treatment plan was biologically optimized at GSI as well as at HIT (Figure 1). About 300 patients with base of skull chordomas and chondrosarcomas have been treated so far. Initially, these patients were treated within a clinical Phase I/II study. This study was able to demonstrate excellent clinical results and carbon ion therapy became approved as the best therapy available in Germany. The actuarial local control rates for the chordoma patients after 3 and 5 years were 80.6% and 70%, the 3 and 5 year overall survival rates were 91.8% and 88.5%, respectively [18].

**Figure 1 F1:**
[figure not shown]
**Typical dose distribution of carbon ion therapy by clivus chordoma patient (axial view and dose legend; red line defines CTV; both eyes, optic nerves and brain steam are also shown)**.

## Methods and Design

### Primary objectives/endpoints of the study

The primary objective of this study is to evaluate, if the innovative therapy (carbon ion irradiation) in chordomas is superior to the standard proton treatment with respect to the Local-progression free survival (LPFS) defined as time from the randomisation to observed local recurrence or death from any cause in the absence of documented local disease progression. Local recurrence defined as MRT or CT - morphological tumour progress in the former irradiated region. A 10% increase in the LPFS is considered clinically relevant assuming that the LPFS rate for the proton therapy is 70%.

### Secondary objectives of the study

1. Assessment of overall survival, progression free and metastasis free survival, patterns of recurrence, local control rate and morbidity.

2. Prognostic factors, definition of patients who will benefit from the adjuvant therapy, risk group definition.

3. Plan quality (target coverage, sparing of organs at risk, integral dose).

### Study design/concept

The study is a double arm prospective randomised clinical phase III study of patients with chordomas of the skull base. Study patients are selected according to the inclusion criteria of the study protocol. After careful review of the patient reports and results of the additional examinations eligibility of a patient is determined. Patients matching the eligibility criteria and willing to participate are registered. These patients are subsequently randomised to one of the two treatment arms (arm A: carbon ion therapy, arm B: proton therapy).

Arm A: carbon ion therapy with a total target dose of 63 Gy E ± 5% to the PTV1 (s. also target definition). The PTV2 will receive a total carbon ion dose of 45 Gy E.

The patients entered in Arm B will receive proton therapy with the same target definition concept. The total proton dose will be 72 Gy E ± 5%. The PTV2 will receive a total dose of 50 to 56 Gy E in conventional fractionation (s. also dose prescription).

Accrual period for the trial will be approximately 5 years. Our study design contains interim analysis after 50% of the predicted events have occurred.

### Inclusion criteria

- Karnofsky Performance Score ≥60%

- Age >18 years and <80 years

- Informed consent signed by the patient

- Histological confirmation of chordoma with infiltration of the skull base.

### Exclusion criteria

- Inability to understand the aims of the study, no informed consent

- Prior RT of skull base region

- Other malignancies with disease-free interval < 5 years (excepting pre-cancerous lesions)

- Participation in another trial

- Pregnancy

- Simultaneous CHT or Immunotherapy.

### Risk group definition

Secondary objectives of the study will be explorative analysed also according to risk groups mentioned in Table 1.

**Table 1 T1:** Risk group characterization

Low-risk	High-risk
Age > 30 years	Age ≤ 30 years
Male chordoma	Female chordoma
No OAR compression	Compression of OAR
Primary tumour	Recurrent tumor
Tumour size < 70 ml	Tumour size > 70 ml

### Randomisation

The randomisation will be done using the on-line randomisation tool (Randomizer.at) which is self-serve and runs exclusively on the Internet. An on-screen form with patient details will be completed. The treatment allocation will be immediately notified. The randomisation will be performed regarding treatment arms A and B. Stratification parameters include the following criteria: age (< 30, ≥ 30 years) and gender.

As this is an open-label study there will be no blinding of treatment assignment.

### Reference Committee

In order to monitor specific aspects of the current trial the Data Monitoring Committee (DMC) will be established. The work of Date Monitoring Committee will be based on the Guideline on Data Monitoring Committees EMEA/CHMP/EWP/5872/03. The DMC will be composed of independent experts in the field of radiation oncology, assessing the progress of the trial and available safety data. The mission of the DMC will be to ensure the ethical conduct of the trial and to protect the safety interests of patients in this trial.

## Radiation therapy

### Immobilisation

Patients will be immobilized using a precision head mask to ensure high repositioning accuracy of the target volume and adjacent structures for carbon ion and proton RT. Safety margins around the clinical target volume (CTV) will be determined individually for each patient. Positioning accuracy will be controlled using orthogonal x-rays or cone-beam-CTs. Set-up deviations will be corrected prior to irradiation by correction with the vector of the robotic table.

### Treatment planning examinations/Target definition

The treatment planning CT (obligate native CT, CT with contrast facultative) and MR - Examination (MRT - compulsory sequences - axial T1 post gadolinium and T2 fat saturated or Flair) will be performed in treatment position using the immobilisation device and will be co-registered. The treatment planning CT will consist of continuous 3 mm slices obtained in a stereotactic or virtual simulation set-up.

The delineation of organs at risk and target volume definition will be done on the basis of CTs and MRI scans. The PTV1 should include the GTV (entire residual tumour) and a 1-2 mm safety margin. PTV2 includes the PTV1 with individual safety margin based on surgical and histological reports, and MR-images to account for subclinical disease. The PTV2 includes the whole clivus and the prevertebral muscles down to the basis of the second cervical vertebra in any case. Normal tissue constrains will be defined as follows: eyes, optic nerves, chiasm, brainstem, spinal cord obligatory, temporal lobes, mandible, salivary glands and others facultatively. An overlap of the PTV and the OAR needs to be avoided.

### Carbon ion/Proton RT

Carbon ion RT planning is performed using the treatment planning software including biological plan optimization for carbon ions. Two to maximum four irradiation fields will be chosen. At HIT the intensity-controlled raster-scan system will be used for beam application. Considering the tolerance dose to organs at risk a dose of 63 Gy E ± 5% in 20-22 fractions for carbon ions and 72 Gy E ± 5% in 34-37 fractions for protons for chordoma patients will be prescribed to the maximum of the calculated dose distribution for the target volume (PTV1). Treatment planning aims at coverage of the PTV1 and PTV2 with the 95%-isodose line of the prescribed dose.

For carbon ion therapy dose specification is based on biologic equivalent dose because of the higher relative biologic effectiveness (RBE) of carbon ions, which differs throughout the target volume due to its dependence on various factors. RBE will be calculated for each voxel throughout the target volumes and biological optimization will be performed. The dose prescription used is related to the isoeffective dose Gy E using daily fractions of 3 Gy E and a weekly fractionation of 4-6 × 3 Gy E.

For proton therapy RBE of 1.1 will be used using daily fractions of 2 Gy E and a weekly fractionation of 4-6 × 2 Gy E.

Evaluation of DVH for the dose distribution will be performed with regards to assess plan quality. Maximum chiasm dose, maximum right and left optic nerves dose, maximum brain steam dose, median brain steam dose, maximum dose to spinal cord, median dose to spinal cord will be reported.

### Dose prescription

Arm A (carbon ion therapy):

Total dose to the PTV2 - 45 Gy E in 3 Gy E/d, 4-6 days a week, 15 fractions

Total dose to the PTV1 - 63 Gy E ± 5%, further 5-7 fractions a 3 Gy E.

Arm B (proton therapy):

Total dose to the PTV2 - 50 to 56 Gy E in 2 Gy E/d, 4-6 days a week, 28 fractions

Total dose to the PTV1 - 72 Gy E ± 5%, further 6-9 fractions a 2 Gy E.

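### The proton-arm PTV2 dose, fraction counts and dose per fraction do not fit together, and some stated combinations fall below the 72 Gy E ± 5% band; the carbon figures are consistent

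*Protocol article*

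**What the plan says.** The protocol article describes the proton regimen in three places.

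- **Study design/concept** gives the PTV1 total as 72 Gy E ± 5% and adds: "The PTV2 will receive a total dose of 50 to 56 Gy E in conventional fractionation".
- **Carbon ion/Proton RT** gives "72 Gy E ± 5% in 34-37 fractions for protons" for PTV1, and fixes the fraction size: "For proton therapy RBE of 1.1 will be used using daily fractions of 2 Gy E".
- **Dose prescription** splits the course into two steps: "Total dose to the PTV2 - 50 to 56 Gy E in 2 Gy E/d, 4-6 days a week, 28 fractions", then "Total dose to the PTV1 - 72 Gy E ± 5%, further 6-9 fractions a 2 Gy E".

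The carbon regimen has the same layout. Carbon ion/Proton RT gives "a dose of 63 Gy E ± 5% in 20-22 fractions for carbon ions". Dose prescription gives "Total dose to the PTV2 - 45 Gy E in 3 Gy E/d, 4-6 days a week, 15 fractions" and then "Total dose to the PTV1 - 63 Gy E ± 5%, further 5-7 fractions a 3 Gy E".

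Under Analysis Populations and General Considerations, the ITT population is primary for efficacy. The per-protocol population excludes selected major deviations that are to be specified in the statistical analysis plan. Secondary efficacy analyses uses the per-protocol population for a sensitivity analysis of LPFS.

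**The concern.** The only planned contrast in this trial is between two radiation regimens, so the figures that define each regimen need to agree. Total dose is the number of fractions times the dose per fraction, which makes agreement easy to check. The carbon lines pass this check. The proton lines fail it at the lower end of the PTV2 range and at the lowest fraction count.

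Two things are at stake. First, the treating team cannot satisfy every stated proton figure at once if it works from the lower PTV2 dose, so the control treatment is not uniquely defined. Second, if the analysis plan counts departure from the ± 5% band as a major deviation, a proton patient treated within the stated fraction counts could be classed as a deviation. Following the carbon counts could not have that result.

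**Working it through.** **Inputs** (all from the protocol article)

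| Item | Carbon | Proton | Section |
|---|---|---|---|
| PTV1 total | 63 Gy E ± 5% | 72 Gy E ± 5% | Carbon ion/Proton RT; Dose prescription |
| Dose per fraction | 3 Gy E | 2 Gy E | same |
| PTV2 dose | 45 Gy E | 50 to 56 Gy E | Study design/concept; Dose prescription |
| PTV2 fractions | 15 | 28 | Dose prescription |
| Further fractions to PTV1 | 5 to 7 | 6 to 9 | Dose prescription |
| Total fractions | 20 to 22 | 34 to 37 | Carbon ion/Proton RT |

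Formulas: total dose = fractions × dose per fraction; band = target × 0.95 to target × 1.05.

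**Carbon, as a check on the reading**

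- PTV2: 15 × 3 = 45 Gy E, as stated.
- Total count: 15 + (5 to 7) = 20 to 22, as stated.
- Total dose: 20 × 3 = 60, 21 × 3 = 63, 22 × 3 = 66 Gy E.
- Band: 63 × 0.95 = 59.85 to 63 × 1.05 = 66.15 Gy E. All three totals are inside.

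**Proton**

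Band: 72 × 0.95 = 68.4 to 72 × 1.05 = 75.6 Gy E.

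The fraction counts reproduce: 28 + (6 to 9) = 34 to 37, so Dose prescription and Carbon ion/Proton RT agree on this.

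(a) *PTV2 line.* 28 × 2 = 56 Gy E only. A PTV2 dose of 50 Gy E would be 50 / 2 = 25 fractions, or 50 / 28 = 1.79 Gy E per fraction over 28. The range, the fraction size and the fraction number cannot all be true.

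(b) *From 50 Gy E.* Adding 6, 7, 8 or 9 fractions of 2 Gy E gives 62, 64, 66 or 68 Gy E, all below 68.4. Reaching the lower limit would take (68.4 − 50) / 2 = 9.2 fractions, more than the stated maximum of 9. If the 50 Gy E is given in 25 fractions, the total count is 31 to 34, which meets the stated 34 to 37 only at 34. If it is spread over 28 fractions, the count agrees but the fraction size is no longer 2 Gy E.

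(c) *From 56 Gy E, the 28-fraction path.*

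| Fractions | Total (Gy E) | Against 72 | In band? |
|---|---|---|---|
| 34 | 68 | −5.6% | No, 0.4 Gy E short |
| 35 | 70 | −2.8% | Yes |
| 36 | 72 | 0.0% | Yes |
| 37 | 74 | +2.8% | Yes |

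**The case against.** The strongest reply is that the coherent path through the text is 28 fractions plus 6 to 9. On that path the counts agree across sections, three of the four totals are inside the band, and the fourth misses by 0.4 Gy E. The PTV1 total of 72 Gy E ± 5% is the figure repeated most consistently, so the treating team would probably be guided by it. All of this stands, and it limits the size of the point. It does not remove the 34-fraction miss, because ± 5% is itself the stated tolerance, nor the conflict inside the PTV2 line.

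One might also suppose that PTV2 receives a smaller daily dose while PTV1 receives 2 Gy E. That would remove (b), but the PTV2 line itself states 2 Gy E per day, and 34 fractions would still fall short.

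A reader might infer more than the text supports:

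- *That the protocol permits proton doses from 62 to 74 Gy E.* It does not. The totals of 62 to 66 Gy E contradict the stated PTV1 total, and they also contradict either the stated fraction counts or the stated fraction size. They show that the figures clash and are not an allowed range.
- *That every course starting from 50 Gy E ends outside the band.* Only the combination of 50 Gy E with 6 to 9 further fractions does so.
- *That control doses will be systematically low and bias LPFS towards carbon.* Nothing in the document shows that the low readings would be used in practice.
- *That sites will differ.* The trial is monocentric.
- *That proton patients will be dropped from the per-protocol set.* The deviations that count are left to a statistical analysis plan that is not shown, and no dose rule is stated.

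**Conclusion.** The point holds as an internal contradiction in the definition of the control arm. It has three parts: the 50 to 56 Gy E range does not fit 28 fractions of 2 Gy E; from 50 Gy E the stated further fractions end 0.4 to 6.4 Gy E below the band (68.4 − 68 and 68.4 − 62); and the lowest stated count, 34 fractions, ends 0.4 Gy E below it. The carbon arm has no such conflict.

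The consequence is ambiguity in the control treatment and, only if dose is among the per-protocol deviations, a risk of misclassifying proton courses in a sensitivity analysis. The ITT primary population, the sample size and the error rates do not depend on these figures.

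The conclusion assumes that the printed fraction size of 2 Gy E applies to every proton fraction, as the text says, and that ± 5% is a limit on the total PTV1 dose. The document does not show which of the conflicting figures is intended.

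**What to change.** The sponsor's clinical team should reconcile the proton figures in Study design/concept, Carbon ion/Proton RT and Dose prescription, so that the PTV2 dose, number of fractions, dose per fraction, further fractions and ± 5% band agree arithmetically. Which figure changes is a clinical decision, and none is proposed here.

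If the analysis plan uses dose as a deviation criterion, each arm should be judged against its own consistent range. One common range cannot serve, because the arms differ in total dose and fraction size.

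The cost is a correction to the protocol text, with no change to the design or the analysis. If treatment has already begun, it also needs an amendment and a check of proton courses already given against the reconciled figures.

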### Dose constraints to organs at risk for both arms

Dose constraints to organs at risk (OAR) are estimated considering the experience of our institution as well as the data reported by Emami et al. [19] (Table 2).

**Table 2 T2:** Dose constraints to organs at risk

OAR	Dose constraints
Eyes, temporal lobes, salivary glands, mandible and other	as low as possible
Optic nerves and chiasm	≤ 54 Gy
Brainstem	≤ 54 Gy with 1% of Volume allowed to receive >54 Gy, with D_max _≤ 60 Gy
Brainstem center	<50 Gy
Spinal cord	≤ 45 Gy with 1% of Volume allowed to receive >45 Gy, with D_max _≤ 50 Gy

## Organization, Workflow and Follow-up

Patient data will be collected and documented pseudonymously using electronic data processing (e.g. patient initials, date of birth and study number) at the study office at HIT. Table 3 presents a brief workflow.

**Table 3 T3:** Workflow time table

Approval of ethics committee
↓
Diagnosis of chordoma of the skull base and completion of pre-radiation treatment examinations (biopsy, operation, staging)
↓
Informed consent of the patient and patient registration by the study office at HIT
↓
Stratification and Randomisation
↓
Arm A: carbon ion RT (63 Gy E ± 5%, fractionation 4-6 × 3.0 Gy E) Arm B: proton RT (72 Gy E ± 5%, fractionation 4-6 × 2.0 Gy E)
↓
Treatment planning for particle therapy
↓
Particle therapy
↓
Follow-up

After randomisation the study number will be assigned.

The following study data will be collected at the study office at HIT:

1. Medical reports including pathology reports and results of staging and additional pre-treatment examinations

2. Documentation of RT (dose distributions and DVH) and position checks

3. Prescribed total target dose and fraction doses, treatment interruptions >4 days

4. Toxicity data

5. Follow-up forms

6. Trial-related documentation including severe AE (CTCAE Grad ≥ 3) will be reported immediately to the study office and the principal investigator of the study

7. The date of local recurrence (MRT or CT - morphological tumour progress in the former irradiated region), distant metastases or death of the patient will be reported and documented.

Local recurrences will be confirmed radiologically and histologically whenever possible. At least two medical doctors (radiation oncologist and/or radiologist) will be required to judge of the recurrence or toxicity.

Every patient is followed for LPFS and trial-related AEs for a time period of 8 years. Furthermore, patients will be followed for survival and locoregional recurrences for a time period of 8 years after completion of the irradiation.

The first and the second follow-up examination will be performed 4-6 weeks and 3 months after completion of RT (follow-up 1 and 2). Follow-up examinations will then be scheduled after 6 months (follow-up 3), 9-12 months (follow-up 4), and then once a year for further 6 years (follow-up 5, 6 and 7). Additional visits will be scheduled as necessary. Acute toxicity is assessed at least weekly during RT and documented at the end of the RT series, 6 weeks after completion of RT and 3 months after RT. Late toxicity will be documented in regular intervals of 6 or 12 months during the observation period. All the patients will be observed for radiation specific acute and late AEs for the time of at least 8 years after irradiation. The maximum grade of toxicity will be determined for each patient.

The Common Terminology Criteria for Adverse Events V4.0 (CTCAE V.4.0) will be used to grade acute toxicity from radiation therapy. The criteria are relevant from the 8th irradiation day until day 90, i.e. until the 1st follow-up visit. Thereafter, the RTOG/EORTC Criteria of Late Effects will be utilized. All acute radiation effects will be documented on an Acute Radiation Effect-Form. In addition, the AE-Form and/or SAE-Form will be filled out. RTOG/EORTC Late Morbidity Scoring Scheme will be used to grade toxicity from radiation therapy occurring later than 90 days after its start, i.e. beyond the 1st follow-up visit. All late radiation effects will be documented on a Late Radiation Effect-Form. In addition, an AE-Form and/or SAE-Form will be filled out, if late radiation effects appear.

The follow-up examinations contain:

- Medical history

- Clinical examination

- MRI or CT of the head

- Documentation of acute side effects/AE (CTCAE V.4.0) up to 90 days after RT

- Documentation of late side effects/AE (RTOG/EORTC) after 90 days after RT

- Reporting/documentation of acute grade 3 or 4 toxicity or grade 3, 4 or 5 late effects.

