### Sample Size Determination

The sample size is calculated on the basis of the following assumptions:

• LPFS rate 5 years after radiation therapy of 70% 1) for proton therapy, hazard λ_1 _= 0.0713, and 80% for carbon ion therapy, hazard λ_2 _= 0.0446 (hazard ratio = 1.599).

• Recruitment period of 5 years, with constant accrual rate of 20% patients per year and a follow-up time of 8 years.

• One interim analysis according to a group sequential design with two stages.

Formula of Schoenfeld [20,21] used for the calculation of the number of accumulated events. For a two-sided logrank test with an overall two-sided significance level of 0.05 (including interim and final analyses) and power of 0.80, 143 events are required. The critical values and the test characteristics of the group sequential test design were calculated for an O'Brien and Fleming type alpha spending function. The computation assumes equal allocation to the two groups (n_2_/n_1 _= 1). Assuming an accrual time of 5 and a maximum observation time of 13 years a total of 319 patients is expected to yield the necessary number of events if the accrual rate is constant. Under these assumptions, the time point of the interim analysis should be 7 years after the first patient is entered. The ADDPLAN, Version 4.0 calculator was used for the sample size estimation. With the assumption that approximately 7% of the patients will be lost to follow-up a total of 344 patients will be needed to accumulate 143 events.

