### Efficacy Analysis

#### Primary efficacy analysis

LPFS is defined as the time from date of randomisation to local recurrence or death from any cause in the absence of documented local disease progression. LPFS will be censored on the date of the last tumour assessment on study for patients who do not have local tumour progression and who do not die while on study.

A log-rank test (two-sided) will be used to compare LPFS between the two treatments. The LPFS-rates will be derived from the Kaplan Meier estimate [22] and the confidence intervals will be calculated using Greenwood's formula.

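### Local recurrence, which probably makes up most of the primary endpoint, is judged on images by two doctors whom the article neither masks to arm nor separates from the treating team

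*Protocol article*

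**What the plan says.** In the protocol article, Primary objectives/endpoints of the study defines the imaging component: "Local recurrence defined as MRT or CT - morphological tumour progress in the former irradiated region". Primary efficacy analysis adds deaths: "LPFS is defined as the time from date of randomisation to local recurrence or death from any cause".

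Organization, Workflow and Follow-up sets the confirmation rule, "Local recurrences will be confirmed radiologically and histologically whenever possible", and then the reader rule, "At least two medical doctors (radiation oncologist and/or radiologist) will be required to judge of the recurrence or toxicity". Randomisation states: "As this is an open-label study there will be no blinding of treatment assignment".

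No section asks that the two doctors be masked, or be outside the team treating the patient. The Data Monitoring Committee described under Reference Committee covers trial progress, safety and ethical conduct. It is given no role in adjudicating endpoints.

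**The concern.** Calling morphological progression in an irradiated skull base involves judgement, and the definition gives no numeric threshold. Histology backs the call only where it can be obtained. As written, two radiation oncologists who treated the patient satisfy the reader rule, and they would know the arm: the schedules differ (20-22 against 34-37 fractions, Carbon ion/Proton RT). With a single centre, no other site dilutes a local reading habit.

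If knowledge of the arm shifts whether or when recurrence is called, the shift enters the log-rank test and the hazard ratio as if it were a treatment effect. Two other rules make an error harder to undo:

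- Under Study duration and interruption criteria, a patient with proven recurrence becomes eligible for other therapy. Continued follow-up is then specified for survival and radiation-specific adverse events, so a premature call may not be corrected from later scans.
- Under Interim Analysis, crossing the boundary at 50% of events has consequences for use of the losing therapy, while follow-up continues. The remaining half of the events could then be read with the interim result known.

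**Working it through.** **The plan's own figures.** Sample Size Determination gives 5-year LPFS of 70% and 80%, with an "overall two-sided significance level of 0.05 (including interim and final analyses) and power of 0.80".

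- Hazard ratio = ln 0.70 / ln 0.80 = 1.598.
- Events (Schoenfeld, 1:1) = 4 × (1.960 + 0.842)² / (ln 1.598)² = 142.7, so 143.
- Patients: with uniform 5-year accrual and 13 years in total, the mean event probability is 0.4487, and 143 / 0.4487 = 318.7, so 319.
- Allowing 7% loss: 319 / 0.93 = 343.01, so 344.

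All three stated figures (143, 319, 344) reproduce. Masked reading changes none of them.

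**Share of events open to reading.** The Background reports for carbon ions: "The actuarial local control rates for the chordoma patients after 3 and 5 years were 80.6% and 70" per cent, and "the 3 and 5 year overall survival rates were 91.8% and 88.5" per cent. At 5 years this is about 30% local failure and 11.5% deaths. If every death came without a prior recurrence, recurrence would be 30 / (30 + 11.5) = 30 / 41.5 = 72% of events. If no event were a death without recurrence, it would be 100%. This is an inference from one earlier series at 5 years; the article gives no event split.

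**Effect of a reading bias.** Assumptions: true hazard ratio 1, 143 events, a relative excess e of recurrence calls in one arm, and recurrence share s. Deaths cannot be shifted by readers, so the excess acts only on the share s.

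- Apparent event ratio r = 1 + e × s
- Shift in the log-rank z = ln(r) × √143 / 2
- Two-sided type I error = 1 − Φ(1.96 − shift) + Φ(−1.96 − shift)

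| Excess e | s = 72%: r, shift, type I error | s = 100%: r, shift, type I error |
|---|---|---|
| 5% | 1.036, 0.21, 5.5% | 1.05, 0.29, 6.0% |
| 10% | 1.072, 0.42, 7.0% | 1.10, 0.57, 8.8% |
| 20% | 1.144, 0.80, 12.7% | 1.20, 1.09, 19.3% |

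The value 1.96 treats the final test as a single look, which is an approximation to the two-stage design.

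**Scale.** With 143 events the final test is significant at an observed hazard ratio of about exp(−1.96 × 2 / √143) = 0.72. Apparent ratios of 1.036 to 1.20 are well short of that alone, but they use up part of the margin.

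**The case against.** **The gap may be one of reporting.** The open-label statement concerns treatment assignment. It does not say how follow-up images are read, and a condensed article may leave reading procedures to the full protocol. A reader might infer that the images are in fact read unmasked by treating doctors, or that bias is present. The document supports neither. What stands is that the article does state a reader rule, and two treating doctors would satisfy it.

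**The size is uncertain.** A reader might take 6.0%, 8.8% and 19.3% as the effect of a 5%, 10% or 20% excess. Those figures hold only if every event is a recurrence, because LPFS also counts deaths; they are upper ends. The model also treats the bias as a lasting proportional excess. Patients are re-imaged repeatedly, so a recurrence missed at one scan may be called at the next, and part of the bias would then be delay.

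**The damage may be reparable.** It is tempting to say that no later analysis could remove such a bias. If the scans are kept, a masked re-read is possible. The article plans none, and it would be the same remedy applied later.

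**Expectation at the site is not clear-cut.** A reader might infer that the centre is judging its own favourable earlier carbon ion results. The Background attributes those results to an initial phase I/II study and places earlier German carbon ion treatment at Darmstadt. It also calls proton therapy the gold standard. The point does not need a presumed motive.

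**Masking is not free or complete.** The article gives no staffing data, so a mandatory non-treating radiologist could mean an extra reader. Masking only the two-doctor step limits overcalling and misdating, but not the undercalling of scans never referred. Reading every scheduled scan masked would mean about 10 visits × 344 patients = 3,440 series, each read twice. These limits are real and shape the remedy; they do not remove the gain from masking readers who are already required.

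**Conclusion.** The point holds as a design weakness worth correcting; it is not a contradiction or an error of calculation. The stated reader rule leaves the main judged component of the primary endpoint unprotected against knowledge of the arm. Type I error would rise from 5% to the ranges in the table, from little more than nominal at a 5% excess to 12.7-19.3% at a 20% excess.

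This rests on three assumptions: the size of the bias, which no document supports at any value; its persistence as a proportional excess; and a recurrence share of 72% to 100%. A smaller share over longer follow-up would lower the figures. Deaths, and histology where obtained, limit the exposure.

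**What to change.** Amend Organization, Workflow and Follow-up as follows:

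- The two doctors already required judge local recurrence on pseudonymised follow-up MRI/CT series, with arm, dose plan and fractionation withheld.
- Neither is a treating physician of that patient, where existing staff allow.
- Their masked decision and the scan date define the imaging event for LPFS. A rule set in advance settles disagreement, and histology is used where obtained.
- Toxicity assessment may stay unmasked.

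The cost is the work of de-identifying image series and assigning readers. The article already requires two judges and pseudonymous documentation, and the event and patient numbers stay at 143, 319 and 344. One limit should be stated openly: masking the confirmation step alone does not catch recurrences that are never referred for judgement.
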